#### 3.3.2 Research Question 1b

With the above mentioned sample size the power is 56–65% ( $n = 128$ –150) to detect a significant difference between high and regular expectation briefing on pain intensity after the acupuncture treatment. This assumption is based on a previous study (Linde et al., 2007) with response rates of 54% in the high expectation group and 39% in the low expectation group that resulted in a SMD of 0.38.

### 3.3.3 Research Question 2

Variation of the outcomes was not known prior to the study. Thus, the sample size was determined using two-group Fisher's exact tests of equal proportions (for binary outcomes). 50% of the patients in the intense safety briefing group and 10% in the regular group were expected to have side effects such that a side effects score can be calculated (Witt et al., 2009). It showed that with 64 patients in each study group such differences in outcome scores could be detected with at least 99% power at a 0.05 two-sided significance level. This power analysis was conservative and the actual power of the study will be higher since a count score and not a binary variable is used.

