### 3.4.2 Research Question 1b

Null hypothesis:

Pain intensity at the end of acupuncture treatment after high efficacy briefing = pain intensity after regular briefing.

The alternative hypothesis is:

Pain intensity at the end of acupuncture treatment after high efficacy briefing  $\neq$  pain intensity after regular briefing.

### 3.4.3 Research Question 2

Null hypothesis:

Side effects after intense side effect briefing = side effects after regular side effect briefing.

The alternative hypothesis is:

Side effects after intense side effect briefing  $\neq$  side effects after regular side effect briefing.

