### 6.2.3 Research Question 2: Side Effects Score at the End of Treatment

As a primary analysis, the side effect scores that are available from up to 7 measurements (before each session, except session 1) will be compared between side effects briefing groups. Covariate of interest thus is the side effects briefing group (`SIDEBRIEF`). The side effect scores will be treated as counts, because they are expected to show a skewed distribution. Because each patient has up to 7 outcome values, a longitudinal zero-inflated negative binomial model will be used. This model will provide increased statistical power with respect to a model with total score as outcome, because it utilizes all outcomes of all patients.

In addition to the briefing group, the linear predictor of the model includes gender (`pers_1_2`) and the time of the measurement since the first session (in days, derived from session dates `verlaufdokua_1b`, `verlaufdokua_2`, ..., `verlaufdokua_8`) as additional fixed effects, and patient-specific random effects for the intercept and time, where the latter accounts for patient-specific dependencies (*i.e.* slopes) on time. The zero-inflation probability will modelled as dependent on `SIDEBRIEF`. The model will be fitted with the `glmmTMB()` function from the R package `glmmTMB` (Brooks et al., 2017). If this longitudinal mixed model fails to converge with the specification given here, the random effect for time will be removed, that is, the dependency on time is then assumed to be the same for all patients.

It will be assumed that missing side effect scores are missing at random (MAR), that is, missingness depends only on observed variables. Importantly, the longitudinal analysis allows for unbalanced data, thus MAR in the outcome is automatically properly accounted for and does thus not require any imputation (Ibrahim and Molenberghs, 2009).

The result from the zero-inflated negative binomial regression will be reported as the ratio of side effect scores (*i.e.*, as the *factor* by which the side effect score changes from regular to intense

side effects briefing) with 95% confidence interval and  $p$ -value. Note that, in this case, a ratio of 1 corresponds to the null hypothesis that there is no effect of `SIDEBRIEF` on the side effect scores. The estimated effects of the adjusting variables will not be shown.

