### 6.6.2 Research question 1b

A second ANCOVA using the pain intensity obtained after the 4th acupuncture session (in week 2) as outcome will be performed. The covariates and adjusting variables will be as described in Section 6.2.2.

### 6.6.3 Research question 2

A secondary outcome for research question 2 is the total side effect score for each patient, which will be adjusted for the number of acupuncture sessions that the patient actually received minus 1. For a patient with the number of sessions given by  $N_s$ , the outcome is thus

$$\text{Total score} = \frac{(\text{Score}_1 + \text{Score}_2 \dots + \text{Score}_{N_s-1})}{N_s - 1} \cdot 7.$$

As this may lead to total score values that are non-integers, the total score will be rounded to the next integer. A zero-inflated negative binomial model with SIDEBRIEF and gender (`pers_1_2`) will be

used. As for the primary analysis (Section 6.2.3), the result from the zero-inflated negative binomial regression will be reported as the ratio of side effect scores with 95% confidence interval and  $p$ -value. In addition, adjusted means of the total side-effects scores with 95% confidence intervals will be reported for each treatment group, where the gender effect will be weighted with 0.5.

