#### 2) Side Effects

We will test null hypothesis:

(2) high side effect briefing = regular side effect briefing for amount of side effects reported

The alternative hypothesis is:

(2) high side effect briefing  $\neq$  regular side effect briefing for amount of side effects reported

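### Research question 2: the SAP does not say how one ratio and one p-value come from a zero-inflated model with two briefing coefficients, and the count coefficient alone would not test the stated null

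*Combined protocol and SAP*

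**What the plan says.** The SAP null hypothesis (3.4.3) concerns the whole outcome: "Side effects after intense side effect briefing = side effects after regular side effect briefing". Protocol 11.1 says the same of the amount reported: "high side effect briefing = regular side effect briefing for amount of side effects reported".

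For the primary analysis, SAP 6.2.3 states that "a longitudinal zero-inflated negative binomial model will be used", using up to seven scores per patient. SIDEBRIEF is in the linear predictor with gender, time and patient random effects. In addition, "The zero-inflation probability will modelled as dependent on" SIDEBRIEF. The briefing therefore has two coefficients.

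The result "will be reported as the ratio of side effect scores", described as the factor by which the score changes from regular to intense briefing, with one 95% confidence interval and one p-value. The SAP adds that "a ratio of 1 corresponds to the null hypothesis that there is no effect of" SIDEBRIEF. It gives no step that combines the two parts, no test of the zero-part coefficient and no joint test.

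The sample size section (SAP 3.3.3) rests on a binary any/none comparison: "50% of the patients in the intense safety briefing group and 10% in the regular group were expected to have side effects". It then says that actual power will exceed the Fisher figure because a count score is analysed.

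**The concern.** In this model family the coefficient that the software prints with a ready standard error is the count-part β. The overall ratio needs a further calculation, which the SAP does not describe, although it does spell out comparable steps elsewhere, such as the weights for adjusted means in 6.2.1 and 6.2.2. An analyst following the text could well report exp(β).

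That quantity compares scores among observations that are not structural zeros. If the intense briefing mainly leads patients to report something where they would otherwise have reported nothing, part of the effect goes into π, and exp(β) can sit near 1. If the additional reports are mild, exp(β) can fall below 1 while total side effects rise. This is one of three primary outcomes, so the conclusion on the nocebo question would depend on an unstated choice.

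**Working it through.** **1. The plan's own power figure.** Inputs from SAP 3.3.3: 50% vs 10%, 64 per group, two-sided 0.05, Fisher's exact test. Enumerating both binomials and summing the probability of all tables that reject gives 0.9991 (normal approximation 0.9995). The stated figure of at least 99% is correct for that binary test.

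**2. What the ratio should be.** With structural-zero probability π and count mean μ, the expected score is (1 − π)μ. Therefore

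overall ratio = exp(β) × (1 − π_intense)/(1 − π_regular).

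This equals exp(β) only if π is the same in both groups, and 6.2.3 lets it differ.

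**3. An illustration with one score per patient.** Assume 10% vs 50% of patients with a score above zero, and negative binomial size 1.5.
- Count means 6 and 6: P(0) in the count part is (1.5/7.5)^1.5 = 0.089. The non-structural shares are 0.10/0.911 = 0.110 and 0.50/0.911 = 0.549. The count ratio is 1.0 and the overall ratio is 5.0.
- Count means 6 (regular) and 4.8 (intense): the intense-group share becomes 0.566. The mean scores are 0.110 × 6 = 0.66 and 0.566 × 4.8 = 2.72. The count ratio is 0.8 and the overall ratio is 4.1.

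**4. Simulated trials in the form of the primary model.** 64 per group, seven scores each, random intercept in the count part, zero part by group, up to 300 fits per scenario. Gender, time and the random slope were left out. Assumed values: size 1.5, random-intercept SD 0.5, regular-group count mean 2 (3 in the third row). The last three columns give the proportion with p < 0.05.

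| π regular → intense | Count ratio | True overall ratio | Count coefficient | Overall ratio (delta method) | Joint 2-df |
|---|---|---|---|---|---|
| 0.60 → 0.40 | 1 | 0.60/0.40 = 1.50 | 4.7% | 69.7% | 96.3% |
| 0.85 → 0.30 | 1 | 0.70/0.15 = 4.67 | 5.7% | 100% | 99.7% |
| 0.70 → 0.30 | 0.7 | 0.7 × 0.70/0.30 = 1.63 | 59.9%, all below 1 | 83.5%, all above 1 | 99.7% |
| 0.50 → 0.50 | 1 | 1.00 | 5.0% | 5.7% | 5.0% |

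Monte Carlo error is about 1.3 points near 5% and 2.8 points near 60%.

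**5. Further runs.** With π 0.70 → 0.50 and count ratio 1, the true overall ratio is 0.50/0.30 = 1.67. The count test rejected in 4% of 120 runs (count mean 2.5, SD 0.6, size 2) and the joint test in 99%. A separate set of 60 fits at a true ratio of 1.67 gave 3% for the count coefficient against 82% for the overall ratio. Another 60 fits at a true ratio of 1.63 gave a count ratio significantly below 1 in 62%.

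**6. Zeros from patients who never report.** The planning rates can instead be generated as 90% vs 50% of patients never reporting (assumed reporter mean 1 per session, SD 0.6, size 2, 60 runs). Fitted with the same model, the count-coefficient test then rejected in 85% of runs (82% upward). The fitted ratio had a median of about 18, against an observed score ratio of 5.2.

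**The case against.** The strongest reply is that the SAP never calls the ratio a count-part ratio. Its verbal definition, read literally, is the overall expected-score ratio. On that reading a ratio of 1 means equal mean scores, and a mean effect is neither missed nor reversed. This stands: count-part only is an inference about implementation. What remains is that the text does not settle which quantity is meant or how its interval and p-value are obtained. Even the overall ratio can equal 1 when the two parts offset each other.

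A second reply is that the count part also generates zeros, and that the 50% and 10% are proportions of patients. The patient random effects sit in the count part, so patients who never report are largely absorbed there and not in π. This also stands, and step 6 of the working shows its force. In the π 0.70 → 0.50 scenario about 84% and 96% of simulated patients had at least one side effect, which is far from the planning rates. The 0.85 → 0.30 row applies the planning rates to sessions, not patients.

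A reader might therefore infer that the stated power falls to about 5%. The documents do not support that. They give no values for π, count mean, dispersion or random-effect SD, and the result depends on where the effect lies.

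Thirdly, SAP 6.6.3 reports adjusted mean total scores by group, so an overall rise would be visible. That helps only in part, because the total score is secondary and protocol 11.3.3 treats secondary analyses as exploratory.

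**Conclusion.** The concern holds in conditional form. The primary estimate and test for research question 2 are not fully specified: two briefing coefficients, one reported ratio, and no stated link between them. If the ratio is the count coefficient, it is not the factor by which the score changes, and its test is not a test of the stated null. Under the assumed parameters it can then miss the effect (about 3–5% rejection with only session-level zeros changing and a true overall ratio of 1.67) or point the wrong way (about 60% significantly below 1 with a true overall ratio of 1.63). The loss may be smaller when zeros come from patients who never report, although the count ratio still misstates the size of the effect there.

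The planning power is right for Fisher's test. The claim that actual power will be higher is not assured for the count coefficient. Type I error is not in question: with no briefing effect in either part, the tests in the table reject in 5.0–5.7% of trials. It would go too far to say that the plan definitely reports the count part alone, or that its primary test necessarily fails.

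**What to change.** In SAP 6.2.3, define the primary estimate and test as the overall expected-score ratio exp(β)(1 − π_intense)/(1 − π_regular). Because π depends on SIDEBRIEF alone, this is a single number from three coefficients: the count coefficient, the zero-part intercept and the zero-part briefing coefficient. Obtain the confidence interval and p-value by the delta method on the log scale from the glmmTMB covariance matrix, or by a bootstrap that resamples patients. Report the count and zero parts as components, so that offsetting effects are visible.

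In 6.6.3, the SAP says that "the result from the zero-inflated negative binomial regression will be reported as the ratio of side effect scores" but not whether the zero part of that model depends on SIDEBRIEF. State this and, if it does, use the same overall ratio.

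Removing SIDEBRIEF from the zero part would make exp(β) the overall ratio, but only by assuming that the briefing does not affect structural zeros, so it is not recommended. A joint 2-df test had more power in some scenarios, but it gives no direction and can reject when the mean scores are equal, so it suits a supporting role.

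In 3.3.3, limit the power statement to the binary comparison. The cost is SAP wording and a few lines of R, with no new data. The definition should be fixed before the allocation is revealed to the analysts.

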### 6.3 Assumptions

The EAT score (baseline and follow-up) and the pain intensity at first visit and follow-up are treated as continuous.

All relevant variables are analyzed graphically by plotting the histograms and boxplots, split by the 2 x 2 groups. The results will be presented in a separate document.

### 6.4 Sensitivity Analyses

#### 6.4.1 Per-Protocol Analyses: Research Questions 1a and 1b

Research questions 1a and 1b will be re-analysed per-protocol as well. Missing values will not be imputed, incomplete cases will be dropped. The models will be the same as described in Sections 6.2.1 and 6.2.2.

#### 6.4.2 Protocol-Deviations: Research Question 1b

Research question 1b will be repeated excluding the patients who used opioids. The analysis of research question 1b will also be repeated including only patients that had at least 6 of the 8 acupuncture treatment sessions.

#### 6.4.3 Extended Models: Research Questions 1a, 1b, and 2

All research questions (1a, 1b, and 2) will also be analyzed using an extended model including age (`age`), duration of pain (`painduration`), depression (`PROMIS_BL_depression.theta`), and CARE score (`CARE_1a_red1`) as additional covariates. Missing values will be imputed.

The follow-up pain intensity (see Section 6.6.5) will be re-analyzed with an extended model as well, including age (`age`), duration of pain (`painduration`), depression (`PROMIS_BL_depression.theta`), and CARE score (`CARE_1a_red1`) as additional covariates. Missing values will be imputed.

Confidence intervals and  $p$ -values from sensitivity analyses are considered explorative.

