### 6.6.6 Perceived Sensitivity to Medicines Score, PSM

The PSM score will be analyzed using three ANCOVA models (no imputation):

```
PSM_8 ~ SIDEBRIEF + pers_1_2 + PSM_BL
```

```
PSM_8 ~ SIDEBRIEF + pers_1_2 + LOT_BL_optim + LOT_BL_pessim +  
acupuncturist + PSM_BL
```

```
PSM_8 ~ SIDEBRIEF + pers_1_2 + LOT_BL_optim + LOT_BL_pessim +  
acupuncturist + age + painduration + CARE_1a_red1 + PSM_BL
```

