#### A.4 Follow-Up With Additional Covariates

```
PROMIS_FU_anxiety.theta ~ EXPBRIEF + pers_1_2 + LOT_BL_optim +  
LOT_BL_pessim + acupuncturist + age + painduration + CARE_1a_red1 +  
PROMIS_BL_anxiety.theta
```

```
PROMIS_FU_depression.theta ~ EXPBRIEF + pers_1_2 + LOT_BL_optim +  
LOT_BL_pessim + acupuncturist + age + painduration + CARE_1a_red1 +  
PROMIS_BL_depression.theta
```

```
PROMIS_FU_fatigue.theta ~ EXPBRIEF + pers_1_2 + LOT_BL_optim +  
LOT_BL_pessim + acupuncturist + age + painduration + CARE_1a_red1 +  
PROMIS_BL_fatigue.theta
```

```
PROMIS_FU_paininterference.theta ~ EXPBRIEF + pers_1_2 +  
LOT_BL_optim + LOT_BL_pessim + acupuncturist + age + painduration +  
CARE_1a_red1 + PROMIS_BL_paininterference.theta
```

```
PROMIS_FU_physfunct.theta ~ EXPBRIEF + pers_1_2 + LOT_BL_optim +  
LOT_BL_pessim + acupuncturist + age + painduration + CARE_1a_red1 +  
PROMIS_BL_physfunct.theta
```

```
PROMIS_FU_sleep.theta ~ EXPBRIEF + pers_1_2 + LOT_BL_optim +  
LOT_BL_pessim + acupuncturist + age + painduration + CARE_1a_red1 +  
PROMIS_BL_sleep.theta
```

```
PROMIS_FU_participation.theta ~ EXPBRIEF + pers_1_2 + LOT_BL_optim +  
LOT_BL_pessim + acupuncturist + age + painduration + CARE_1a_red1 +  
PROMIS_BL_participation.theta
```

```
promis_fu_29 ~ EXPBRIEF + pers_1_2 + LOT_BL_optim + LOT_BL_pessim +  
acupuncturist + age + painduration + CARE_1a_red1 + promis_1a_29
```

```
nrs_fu_2 ~ EXPBRIEF + pers_1_2 + LOT_BL_optim + LOT_BL_pessim +  
acupuncturist + age + painduration + CARE_1a_red1 + nrs_1a_2
```

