## B Glossary of Variable Names

| Variable name                    | Variable explanation                                                         | Timepoint                                   | Minimum   | Maximum                |
|----------------------------------|------------------------------------------------------------------------------|---------------------------------------------|-----------|------------------------|
| EAT_BL                           | Expectation about Acupuncture Treatment Baseline Score                       | Baseline                                    | 5         | 20                     |
| screeningb_1a_4a                 | pain intensity (at first visit)                                              | Baseline                                    | 0         | 10                     |
| nrs_1a_2                         | pain bothersomeness                                                          | Baseline                                    | 0         | 10                     |
| painduration                     | pain duration (at first visit)                                               | Baseline                                    | 3         | 600                    |
| LOT_BL_optim                     | Life Orientation Test - optimism score                                       | Baseline                                    | 0         | 12                     |
| LOT_BL_pessim                    | Life Orientation Test - pessimism score                                      | Baseline                                    | 0         | 12                     |
| age                              | age in years                                                                 | Baseline                                    | 18        | 65                     |
| pers_1_2                         | gender                                                                       | Baseline                                    | 1 female  | 2 male                 |
| CARE_1a_red1                     | CARE score (without item 9)                                                  | Baseline                                    | 8         | 41                     |
| promis_1a_29                     | PROMIS pain intensity                                                        | Baseline                                    | 0         | 10                     |

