### **9.2.3 Additional measures:**

We measure the optimism with the Life-orientation Test (LOT-R), (Glaesmer et al., 2008) at baseline.

Empathy of the physician: We will measure empathy using the German Version of the "Consultation and Relational Empathy" (CARE) instrument (Neumann et al., 2008). The CARE is a one dimensional measure that consists of 9 items with a 5 point Likert scale. We will ask patients to complete it after the briefing and before the first acupuncture session.

Post-treatment guess: After completion of treatment, acupuncture therapists will be asked to guess which interventions patients received and their confidence with this guess. This will allow checking whether treatment providers were successfully blinded to briefing assignments.

Patients will be also asked to guess which briefing interventions they received. The patient guesses will be obtained after disclosure of the study aim at the end of the study (see ethical considerations), which might inform us about the success of the experimental manipulation.

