### **9.3.2 Baseline (Visit 1a)**

The first visit will take place at the Institute of Complementary and Integrative Medicine. The patient will be asked to hand in the informed consent for study phase 1 he had signed after the telephone interview and the baseline questionnaire to the study center. The study center will check them for completeness.

From the physician, the patient will receive the patient information for study phase 2 (B2) and will be asked to read it carefully.

Thereafter, the physician will inform the patient in detail about the study. The patient will have the opportunity to ask questions concerning the second phase of the study. The second informed consent will be given to the patient and he will be asked to read and sign it if he or she is still interested to participate in the study.

The physician will then check the inclusion criteria (See B1: demographic data, pain duration and severity ( $\geq 4$  NRS), health status and patients' medical history/comorbidity).

The appointments fixed at the first phone screening will be provided to the physician by the study center. The physician and the patient will go through all the appointments to confirm that the patient can come for acupuncture on all dates.

In case of inclusion, the physician will assign the patient to a group allocation via secuTrial.

Afterwards, the briefing will take place for around 30 minutes. In the course of this briefing, material will be provided to the patient to take home (see brochures).

In addition the physician will give the patient the EAT (P2) and CARE (P4) and ask him to complete them immediately and to hand out P2 and to put P4 into an envelope. The physician will meanwhile fill in the adherence questionnaire B4.

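### CARE is labelled a baseline covariate but is rated after the randomised briefing, so the exploratory models that adjust for it need not estimate the total briefing effect

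*Combined protocol and SAP*

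**What the plan says.** **Where CARE is used.** SAP 6.4.3 extends the models for 1a, 1b, 2 and follow-up pain with age, pain duration, depression "and CARE score (`CARE_1a_red1`) as additional covariates". All nine models in Appendix A.2 and all nine in A.4 contain it (in A.4, for example, "LOT_BL_pessim + acupuncturist + age + painduration + CARE_1a_red1"), and so does the third PSM model in SAP 6.6.6 ("acupuncturist + age + painduration + CARE_1a_red1 + PSM_BL"). That makes 4 + 9 + 9 + 1 = 23 models. SAP 6.5 and 6.6.5 also list CARE as an imputation predictor.

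**When it is measured.** Protocol 9.3.2 sets the order at visit 1a. First comes allocation: "In case of inclusion, the physician will assign the patient to a group allocation via secuTrial". The briefing of about 30 minutes follows. Then: "In addition the physician will give the patient the EAT (P2) and CARE (P4) and ask him to complete them immediately". Protocol 9.2.3 agrees: "We will ask patients to complete it after the briefing and before the first acupuncture session".

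**What it rates.** According to protocol 5.3, it rates the empathy of the physician who carries out the briefing.

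**How the SAP labels it.** The glossary in Appendix B gives `CARE_1a_red1` the time point Baseline. It gives `EAT_1b`, completed at the same sitting, a time point after the intervention.

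**The concern.** Age, pain duration and baseline depression are fixed before the briefing. Adjusting for them can sharpen the estimate without changing what it estimates. CARE is different: it is the patient's reaction to the conversation being tested, and it is recorded at the same moment as the 1a outcome. If a briefing moves CARE and CARE is associated with the outcome within arms, the coefficient for briefing group in the extended model is no longer the total effect that the primary model estimates.

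Interpretation is what is at stake. The extended models stand among the sensitivity analyses, so a difference from the primary result could be taken as a sign that the primary result is fragile, when the two models are answering different questions. The glossary label adds to this. SAP 5.5, on baseline characteristics, summarises every analysis variable by randomised group, so a difference in CARE produced by the briefing could pass for chance imbalance.

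**Working it through.** **Timing.** The glossary puts `CARE_1a_red1` at Baseline and `EAT_1b` after the intervention, whereas protocol 9.3.2 has both forms handed over together once the briefing is done. Both are therefore post-randomisation measures, and the glossary entry for CARE does not match the protocol.

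**The plan's own effect sizes.** SAP 3.3.1 assumes SMD 0.5 for 1a, with 64 per briefing level and 80% power at two-sided 5%. The noncentral t distribution gives 80% power at 64 per arm (0.8015), so the figure reproduces. For 1b (SAP 3.3.2), SMD 0.38 gives 56.9% at 64 per arm and 63.8% at 75 per arm, against the stated 56–65%. These figures are not in dispute; they serve as the total effects below.

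**Formula for the ANCOVA models.** Code the outcome so that a positive difference favours the high briefing, and set within-arm SDs to 1. Let *a* be the shift in CARE caused by the briefing, in SDs, and *r* the within-arm correlation of CARE with the outcome. With group G, CARE = aG + e and Y = total × G + r × e + independent noise. Substituting e = CARE − aG gives

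adjusted effect = total effect − a × r.

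This holds whether *r* arises because CARE influences the outcome or because some patient trait drives both.

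**Results.** The documents give neither *a* nor *r*; every value below is assumed.

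| a | r | 1a: 0.50 − a×r | 1b: 0.38 − a×r |
|---|---|---|---|
| 0 | any | 0.50 | 0.38 |
| 0.2 | 0.2 | 0.46 (−8%) | 0.34 (−11%) |
| 0.3 | 0.3 | 0.41 (−18%) | 0.29 (−24%) |
| 0.5 | 0.5 | 0.25 (−50%) | 0.13 (−66%) |
| −0.3 | 0.3 | 0.59 (+18%) | 0.47 (+24%) |

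A simulation with 64 per arm and 4,000 runs per scenario agrees: for a total effect of 0.50, the mean adjusted estimate is 0.408 at a = r = 0.3 and 0.252 at a = r = 0.5. With no total effect and a = r = 0.3 it is about −0.09 rather than 0.

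**Precision.** With n = 64 per arm, SE = √(1 − r²) × √(2/n) × √(1 + a²/4). For 1a with r = 0.3, power is 84% at a = 0 and 67% at a = 0.3. Adjusting for CARE gains a little power if the briefing leaves CARE alone, and loses power if the briefing moves CARE in the direction that attenuates the effect.

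**Scope.** SAP 6.2.1 to 6.2.3 define the primary models, and none contains CARE. The SMD arithmetic does not carry over to research question 2, which reports a ratio from a zero-inflated negative binomial model. The same reasoning applies there, but no size is claimed.

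**The case against.** - **No shift in CARE is documented.** A reader might infer that the extended models do remove part of the briefing effect, because one script is warmer than the other. The documents do not support that. CARE is taken after the first briefing only, where the contrast is mainly one of information. The clearest differences in reassurance belong to the booster visit, which comes later. Protocol 8.1 has the briefing doctors trained in an empathic communication style, and protocol 3.6 says that regular-briefing patients will not be discouraged. No mechanism is described for the side effects briefing either, beyond its different content. This stands: a shift is plausible but not shown, and its sign is open.
- **The protocol foresaw the covariate.** Section 11.3.2 names empathy among example covariates for sensitivity analyses. This stands as a reason to record any removal. It does not address the timing, which neither document discusses.
- **Nothing confirmatory depends on it.** SAP 6.4.3 calls sensitivity results explorative, protocol 11.3.3 does the same for secondary analyses, and the gate from 1a to 1b uses the primary models. This stands in full and limits the weight of the point.
- **The label follows the visit name.** Visit 1a is called Baseline in the protocol, and the study schedule places CARE in that column. That explains the entry, but the glossary separates `EAT_1b` from baseline at the same sitting, so CARE should be treated alike.

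**Conclusion.** The point holds in a conditional form. CARE is a post-randomisation rating of the person who delivers the intervention, and the glossary time point is wrong by the protocol's own sequence. The 23 models that adjust for it need not estimate the total briefing effect, and neither document says that they target anything else. Whether they depart from it, and in which direction, depends on two quantities that the documents do not give. Under the assumed values, an SMD of 0.50 could read anywhere from 0.25 to 0.59, and it stays at 0.50 if the briefing leaves CARE unchanged. A reader might also infer that the 1a or 1b conclusion is compromised. It is not: the primary analyses and the hierarchical test do not use CARE. Its use as an imputation predictor is not a fault, since post-randomisation variables may serve there.

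**What to change.** 1. In SAP Appendix B, change the time point of `CARE_1a_red1` to after the briefing.
2. Remove CARE from the covariates in SAP 6.4.3, A.2, A.4 and the third PSM model, and leave each model's other covariates as they are. The lists differ: depression is an added covariate in 6.4.3, but not in A.2, A.4 or the PSM model.
3. Record the removal as a departure from the example list in protocol 11.3.2. The SAP is dated 29 May 2018, after the last patient visit on 11 December 2017, so the reason should be written down before the analysis is run.
4. If a CARE-adjusted version is kept, report it beside the CARE-free version and label it a mediation or direct-effect analysis, not a robustness check. State that this reading assumes no unmeasured trait drives both CARE and the outcome.
5. Keep CARE as an imputation predictor. If wanted, compare it between briefing groups as a process outcome, which would also show whether the shift assumed above exists.

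The cost is a short SAP revision, one term fewer per model and a small documented deviation. No new data are needed.
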